## Abstract

**Background:**

Heavy menstrual bleeding is an important health problem. Two frequently used therapies are the levonorgestrel intra-uterine system (LNG-IUS) and endometrial ablation. The LNG-IUS can be applied easily by the general practitioner, which saves costs, but has considerable failure rates. As an alternative, endometrial ablation is also very effective, but this treatment has to be performed by a gynaecologist. Due to lack of direct comparison of LNG-IUS with endometrial ablation, there is no evidence based preferred advice for the use of one of these treatment possibilities.

**Method/design:**

A multicenter randomised controlled trial, organised in a network infrastructure in the Netherlands in which general practitioners and gynaecologists collaborate.

Women ≥ 34 years with heavy menstrual bleeding, a Pictorial Blood Assessment Chart (PBAC) score exceeding 150 points and no future child wish can participate in the trial. After informed consent, women will be randomised to a strategy starting with a levonorgestrel releasing intrauterine system or a strategy starting with endometrial ablation.

The primary outcome is the PBAC score at 24 months of follow-up. Secondary outcomes are patient satisfaction, complications, number of re-interventions, menstrual bleeding pattern, quality of life, sexual function, sick leave and costs. As predictors of effect of intervention we also meaure level of coagulation factors.

**Discusson:**

This study, considering both effectiveness and cost effectiveness of LNG-IUS versus endometrial ablation may well improve care for women with heavy menstrual bleeding.

**Trial registration:**

Dutch trial register, number NTR2984

## Background

Heavy menstrual bleeding is a frequent problem that affects many premenopausal women in the Netherlands and is the most important reason for a visit a the outpatient department of gynaecology [1,2]. Each year one in 20 women between 30 to 49 years of age consult their general practitioner (GP) with heavy menstrual bleeding. Hormonal treatment with the oral contraceptive pill or the levonorgestrel releasing intra uterine system (LNG-IUS) or non-hormonal treatment with tranexamic acid or non-steroidal anti-inflammatory drugs (NSAID) are advised as treatments of first choice. Nevertheless 77% of the women are not willing to continue their treatment and often end up undergoing other treatment or even surgery [3,4].

Hysterectomy is a definitive solution for the treatment of heavy menstrual bleeding, and in 2010 11,038 women underwent a hysterectomy due to bleeding disorders in the Netherlands [5]. Recently it was reported that hysterectomy should be considered the preferred strategy for the treatment of heavy menstrual bleeding based on cost-effectiveness [6]. Nevertheless, it is a major surgical procedure and has significant physical complications and social and economic costs [7]. A significant number of women with heavy menstrual bleeding who seek treatment will not benefit from, or will not wish to continue the medical treatment and are keen to preserve their uterus [3,8]. Many women opt for a less invasive treatment, even when they are informed of the fact that success is not always assured [1,9].

Two frequently used minimally invasive treatment options for heavy menstrual bleeding are the LNG-IUS and endometrial ablation.

Intrauterine devices were initially introduced as contraceptives, but after the addition of progestagen (LNG-IUS) these devices also reduce menstrual bleeding effectively. The local release of levonorgestrel in the uterine cavity suppresses endometrial growth. A systematic review on the effectiveness of the LNG-IUS in heavy menstrual bleeding concluded that the reduction of menstrual blood loss was 79-96% in the LNG-IUS group [10-13]. In women with heavy menstrual bleeding who presented to primary care providers, the LNG-IUS was more effective than usual medical treatment in reducing the effect of heavy menstrual bleeding on quality of life [14]. However, up to 60% of women discontinue LNG-IUS within 5 years because of unscheduled bleeding, pain, and/or systemic progestogenic side-effects [15]. In the Royal College of Obstetricians and Gynaecologists (RCOG) guideline on heavy menstrual bleeding, the use of the LNG-IUS is the first therapeutic option when drug treatment has failed. This is not based on proven cost-effectiveness [15].

Endometrial destruction techniques, which aim to destroy or remove the endometrial tissue, have become alternatives to hysterectomies. In 1991 in the Netherlands 21,433 hysterectomies were performed, a number that was reduced to 16,320 in 1998 and just above 11,000 in 2010, which was partly due to the start of using endometrial ablation [16]. Approximately 47-58% percent of women report an amenorrhea after treatment with the bipolar ablation device [5,17-20]. The satisfaction rates of endometrial ablation have been evaluated by several randomised controlled trials and is showing a rate of about 90% [19,21,22]. Ablation techniques result in shorter duration of surgery, shorter hospital stay and quicker recovery time compared to hysterectomy.

Seven trials compared the LNG- IUS with transcervical resection of the endometrium or balloon abaltion. In the meta-analyses a significant lower mean pictorial blood chart score (PBAC) was reported for all women and a significant lower mean reduction in pictorial blood chart score was reported in the surgical group. One study showed a significantly lower median PBAC score in the LNG-IUS group at nine months and one year follow-up 23. Further outcomes showed no difference in satisfaction rates, amenorrhea rates, duration of menstruation, further surgical treatment or quality of life (QoL). Nevertheless, the studies are small, most studies have a short period of follow-up and contain a lot of non-compliance, which makes interpretation of outcomes difficult [12,20,23-27].

Consequently, usual care in the Netherlands implies one of these two strategies for the treatment of heavy menstrual bleeding if drug therapy fails. The strategy LNG-IUS means prescription and placement by the general practitioner (GP) or gynaecologist without anaesthesia. The strategy endometrial ablation implies performing an endometrial ablation by a gynaecologist in day-care or outpatient clinic with or without general anaesthesia. Due to lack of sufficiently powered studies directly comparing LNG-IUS with endometrial ablation, there is currently no evidence based advice for the use of one of these treatment possibilities.

We propose a randomised controlled trial in which these two strategies are compared in the treatment of heavy menstrual bleeding. The study will focus on (cost-) effectiveness, patient satisfaction and QoL.

## Methods/design

### Objective

The aim of this study is to assess the effects and cost-effectiveness of a strategy starting with LNG-IUS versus a strategy starting with endometrial ablation in women with heavy menstrual bleeding. This study will also evaluate QoL, sexual function and as predictors of effect of intervention we also measure level of coagulation factors.

### Trial design

This study is a multicenter randomised controlled trial with an economic evaluation alongside it. It will be performed by the Dutch Consortium for Studies in Women’s Health and the department of General Practice of the University Medical Center Groningen. The study will be organized in a network infrastructure in which GPs and gynaecologists collaborate. Participating hospitals can be district, teaching, third referral or university hospitals. The study is conducted according to the principles of the Declaration of Helsinki and in accordance with the Medical Research Involving Human Subjects Act (WMO) and has been approved by the ethics committee of the Academic Medical Centre Amsterdam (ref. no MEC 10/183). The protocol is registered in the Dutch trial register, number NTR2984.

### Eligibility criteria

Women ≥ 34 years suffering from heavy menstrual bleeding, with a PBAC score exceeding 150 points can participate in the trial.

Women who might want to get pregnant in the future will be excluded as an endometrial ablation is an absolute contraindication for pregnancies. Other exclusion criteria are abnormal cervix cytology in the past 5 years, a sounding length of more than 10 cm, intracavitary fibroids or polyps or large intramural fibroids determined by either a transvaginal ultrasound (TVU) or a bimanual vaginal examination.

### Patient recruitment, randomization and collection of data

Eligible patients are identified by the gynaecologist in the participating hospitals or by participating general practitioners. Before entry into the study, inclusion and exclusion criteria are checked by research nurses and if women are eligible they will also be counseled by these experienced research nurses. They will be informed about the aims, methods, reasonably anticipated benefits and potential hazards of the study. We will ask separate informed consent for taking and analyzing blood on levels of coagulation factors. After given written informed consent women will be randomised to a strategy starting with a LNG-IUS or a strategy starting with endometrial ablation. Randomisation is performed by accessing a web-based randomisation program. We will stratify for inclusion by general practitioner or by gynaecologist. Patients will be randomised into two groups in a ratio of 1:1, using permuted block randomization with a variable block size.

Participants will be given a computer generated numeric code. Data handling will be done anonymously, with the patient code only available to the local investigator and the research nurse working in the local centre. At the local centres, baseline data and follow-up data collection is the responsibility of the specialised research nurse. Data will be collected using a website dedicated to studies in the Dutch Consortium for women’s health and reproductive medicine studies (http://www.studies-obsgyn.nl). In accordance with guidelines of the Dutch Federation of University Medical Centres (NFU) the data will be kept for 20 years.

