### Measurements and follow-up

Before randomization patients are asked to fill out a PBAC. Prior to start of the treatment, participating patients will fill in two questionnaires measuring health-related QoL: the Short Form-36 (SF-36), a validated GP and the Shaw heavy menstrual bleeding questionnaire, a disease specific questionnaire, which we validated linguistically. Furthermore, patients are asked to complete questionnaires to measure sexual functioning: the Female Sexual Function Index (FSFI), Female Sexual Distress Scale (FSDS) and a questionnaire to measure (indirect) costs. Baseline demographic characteristics, medical history and menstruation pattern are recorded in a Case Record Form (CRF).

Patients will fill in the PBAC and the same questionnaires used at baseline at 3, 6, 12 and 24 months after randomised. Since we compare strategies starting with LNG-IUS or endometrial ablation, patients who are not satisfied with the (randomised) treatment effect can choose another treatment, or opt for hysterectomy. Nevertheless, they will be asked to complete follow-up questionnaires.

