### Outcome measures

Primary outcome is the PBAC score at 24 months of follow-up. Secondary outcomes are patient satisfaction, complications, number of re-interventions, menstrual bleeding pattern, including rates of amenorrhea, QoL, sexual function, sick leave and costs and as predictors of effect of intervention we also measure level of coagulation factors.

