### Statistical analysis

#### Sample size

The study is designed as a non-inferiority study. Based on previous studies, we estimate the mean PBAC score at 24 months of follow-up to be 50 points in the LNG-IUS group and 40 points in the endometrial ablation group, with a SD of 40 [23-26].

Previous studies in women with heavy menstrual bleeding have shown that a 50 point difference in PBAC –score between treatments represents a clinically meaningful difference in reduction of menstrual bleeding. In our study we use a non-inferiority marge of 25 points. With this marge and estimated mean PBAC-scores of 50 and 40 points in resp. the LNG-IUS and endometrial ablation group, the estimated scores in both treatment groups will be far below the upper range of normal menstrual blood loss. Using a dropout rate of 15%, an alpha error of 2.5% and Beta error of 20%, we need to include 266 patients (133 patients per treatment group).

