#### Data analysis

Data will be analysed according to the intention to treat principle. Statistical analysis will be performed using the software Statistical Package for the Social Sciences (SPSS, Inc., Chicago, IL, USA).

Point estimates and 95% confidence intervals will be calculated for different time points.

First, the treatment effect at 24 months of follow-up of a strategy starting with LNG-IUS compared to a strategy starting with endometrial ablation will be investigated. For not normally distributed continuous variables, differences between groups will be tested with the Mann–Whitney U test. Differences between categorical variables will be tested with the Chi-square test or Fisher’s exact test. Secondary, to assess the treatment effect over time, and the interaction of the intervention effect, we will use a mixed effects model. Time to re-intervention will be compared with Kaplan Meier analysis and Cox regression.

The analysis of the influence of lower levels of coagulation on the treatment effect of LNG-IUS and endometrial ablation will be explorative.

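### The only 24-month test named for a skewed outcome, Mann–Whitney U, can use neither the randomisation stratum nor baseline PBAC and gives no mean difference for the 25-point margin

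*Protocol article*

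**What the plan says.** On allocation, the section on recruitment and randomisation states "We will stratify for inclusion by general practitioner or by gynaecologist" and "Patients will be randomised into two groups in a ratio of 1:1, using permuted block randomization with a variable block size".

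On baseline, *Measurements and follow-up* states "Before randomization patients are asked to fill out a PBAC". *Eligibility criteria* admits women "with a PBAC score exceeding 150 points can participate in the trial", so a baseline score should exist for everyone randomised.

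On the target, *Outcome measures* states "Primary outcome is the PBAC score at 24 months of follow-up". *Sample size* adds "The study is designed as a non-inferiority study", with a margin of 25 points and expected means of "50 points in the LNG-IUS group and 40 points in the endometrial ablation group, with a SD of 40".

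On analysis, *Data analysis* promises point estimates and 95% confidence intervals at the different time points, without describing the method behind them. It puts the 24-month treatment effect first and continues: "For not normally distributed continuous variables, differences between groups will be tested with the Mann–Whitney U test". A mixed effects model follows as a secondary step, for the effect over time. No covariates are listed for it.

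**The concern.** The trial holds two pieces of baseline information that may bear on the primary outcome: the setting on which randomisation is stratified, and the baseline value of the outcome itself. The one 24-month test named for a non-normal continuous variable can use neither. It also compares ranks, whereas the margin and the sample size are in mean PBAC points.

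Precision matters here because the design has little slack. The expected difference is 10 points and the margin is 25, which leaves 15 points against a standard error of about 5.3. Precision gained from data already collected would directly raise the chance of a clear non-inferiority conclusion.

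**Working it through.** **Inputs.** From *Sample size*: margin 25, means 50 and 40 (difference 10), SD 40, alpha 2.5%, power 80%, dropout 15%. The side of alpha is not stated; one-sided is assumed, and this reproduces the plan's figure. Two quantities are not in the document and are assumptions shown as ranges: the correlation r between baseline and 24-month PBAC, and the share s of outcome variance explained by recruiting setting.

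**1. The plan's own figure.** For an unadjusted difference in means, n = 2 × 40² × (1.960 + 0.842)² / (25 − 10)² = 111.6, so 112 per arm. Then 112 / 0.85 = 131.8, so 132 per arm and 264 in total. With the t distribution, n = 113 and 113 / 0.85 = 132.9, so 133 per arm and 266 in total, exactly as stated.

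**2. Is the Mann–Whitney condition likely to be met?** A normal distribution with mean 40 and SD 40 would put Φ(−40/40) = 15.9% of women below zero. With mean 50 it would put Φ(−50/40) = 10.6% there. PBAC cannot be negative, so the planned values imply skewness. *Background* also cites amenorrhoea in 47–58% of women after bipolar ablation, which suggests many scores at or near zero in that arm. On the plan's own figures the condition is likely to be met.

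**3. Precision without adjustment.** SE = 40 × √(2/113) = 5.32. The 95% half-width is 1.96 × 5.32 = 10.43. Power = Φ(15/5.32 − 1.96) = Φ(0.859) = 80.5%.

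**4. Adjusting for baseline PBAC.** Residual SD = 40 × √(1 − r²), put into the same formulas:

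| Assumed r | Residual SD | 95% half-width | Power, 113 per arm | Total N for 80% power (normal approximation, 15% dropout) |
|---|---|---|---|---|
| 0 | 40.0 | 10.43 | 80.5% | 264 |
| 0.1 | 39.8 | 10.38 | 80.9% | 262 |
| 0.2 | 39.2 | 10.22 | 82.0% | 256 |
| 0.3 | 38.2 | 9.95 | 84.0% | 240 |
| 0.5 | 34.6 | 9.03 | 90.2% | 198 |

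These figures compare means. They show what adjustment adds to an unadjusted mean comparison, which is also what the plan's N assumes. They do not measure the power of Mann–Whitney itself.

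**5. Adjusting for the stratum.** Stratified blocks balance setting across arms, so the true SE shrinks by √(1 − s), while the unadjusted formula still counts the between-setting variance. One-sided type I error is then about Φ(−1.96/√(1 − s)): 2.2% for s = 5% and 1.9% for s = 10%, against a nominal 2.5%.

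A simulation agrees. It used 113 per arm, two equal strata, assumed block sizes of 2, 4 and 6, and normal outcomes, with 10,000 trials at the margin and 5,000 at a true difference of 10:

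| s, r | Type I error, unadjusted / adjusted | Power, unadjusted / adjusted |
|---|---|---|
| 0, 0 | 2.3% / 2.4% | 80.0% / 80.1% |
| 5%, 0.3 | 2.2% / 2.5% | 80.5% / 85.6% |
| 10%, 0.3 | 1.7% / 2.2% | 81.9% / 88.0% |
| 10%, 0.5 | 2.0% / 2.7% | 81.8% / 93.3% |

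The Monte Carlo error at 2.5% is √(0.025 × 0.975 / 10,000) = 0.16 percentage points. The adjusted interval stays near nominal, and the unadjusted interval is never anti-conservative.

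**The case against.** A reader might infer that the plan fixes an unadjusted primary analysis and throws both variables away. The text does not say so. The Mann–Whitney rule is conditional and covers continuous variables in general. The method behind the promised confidence intervals is not described, and the mixed model's covariates are simply not listed. A journal article commonly leaves a covariate list to the full protocol or SAP, neither of which is shown. That objection stands. For the same reason, no criticism is made of the covariates in the Cox model or in the analyses of secondary outcomes.

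A reader might also infer that chance imbalance in baseline bleeding would bias the result. It would not. Under randomisation the unadjusted comparison is unbiased, and its standard error already allows for chance imbalance. Adjustment sharpens the estimate.

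The gain may also be small. Entry above 150 points restricts the baseline range, many 24-month scores may be near zero, and women may change treatment during follow-up. All of these could weaken the correlation.

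One part of the concern survives. The article names a test, its own figures make that test likely to apply to the primary outcome, and the test cannot take a covariate. A stratified rank test could handle the setting, but none is named, and it would still give no mean difference in PBAC points.

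**Conclusion.** The point holds as one of efficiency and of fit to the margin. The 24-month test named for a skewed outcome can use neither the stratification factor nor baseline PBAC, and it does not produce the quantity in which the margin is set.

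If the two variables are prognostic, leaving them out loses precision. Leaving out the stratum also makes the interval mildly conservative: simulated one-sided error was 1.7–2.2% when setting explained 5–10% of the variance. The stated 266 remains correct for an unadjusted comparison of means and gives its 80% power.

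The size of the gain is uncertain. From baseline PBAC alone it is under 2 percentage points of power if r is 0.2 or less, about 3.5 points at r = 0.3, and nearly 10 at r = 0.5. The document supports no particular value of r or of s. This is a worthwhile improvement at no cost, not a flaw that threatens validity.

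**What to change.** Name one primary 24-month analysis: a linear model for PBAC in points, or the 24-month contrast from a mixed model, with terms for treatment, baseline PBAC and GP/gynaecologist stratum. Use robust or bootstrap standard errors to allow for skewness. Base the non-inferiority conclusion on the upper limit of the 95% confidence interval for the adjusted mean difference (LNG-IUS minus ablation) against 25 points. Keep Mann–Whitney as a supportive analysis.

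The cost is a change of wording, made before 24-month data are compared by arm. The stratum is known from randomisation and baseline PBAC from eligibility screening, so no new data are needed. The sample size need not change, and it would be unwise to reduce it on an assumed correlation.

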### Interventions

The LNG-IUS can be placed either by a GP or by a gynaecologist. In the endometrial ablation group, a second generation bipolar ablation technique (Novasure) will be performed by a gynaecologist.

### Measurements and follow-up

Before randomization patients are asked to fill out a PBAC. Prior to start of the treatment, participating patients will fill in two questionnaires measuring health-related QoL: the Short Form-36 (SF-36), a validated GP and the Shaw heavy menstrual bleeding questionnaire, a disease specific questionnaire, which we validated linguistically. Furthermore, patients are asked to complete questionnaires to measure sexual functioning: the Female Sexual Function Index (FSFI), Female Sexual Distress Scale (FSDS) and a questionnaire to measure (indirect) costs. Baseline demographic characteristics, medical history and menstruation pattern are recorded in a Case Record Form (CRF).

Patients will fill in the PBAC and the same questionnaires used at baseline at 3, 6, 12 and 24 months after randomised. Since we compare strategies starting with LNG-IUS or endometrial ablation, patients who are not satisfied with the (randomised) treatment effect can choose another treatment, or opt for hysterectomy. Nevertheless, they will be asked to complete follow-up questionnaires.

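### Baseline quality-of-life, sexual-function and cost questionnaires are required only before treatment starts, so they may be completed after the woman knows her allocation

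*Protocol article*

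**What the plan says.** All references are to the protocol article.

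- **Measurements and follow-up, PBAC:** "Before randomization patients are asked to fill out a PBAC".
- **Same paragraph, SF-36 and Shaw:** "Prior to start of the treatment, participating patients will fill in two questionnaires measuring health-related QoL".
- **Same paragraph, FSFI, FSDS and cost questionnaire:** "Furthermore, patients are asked to complete questionnaires to measure sexual functioning". The sentence also covers the cost questionnaire and sets no time point.
- **Next paragraph, follow-up:** "Patients will fill in the PBAC and the same questionnaires used at baseline at 3, 6, 12 and 24 months after randomised". The questionnaires are therefore treated as baseline measurements, and the follow-up clock starts at randomisation.
- **Patient recruitment, randomization and collection of data:** "After given written informed consent women will be randomised to a strategy starting with a LNG-IUS or a strategy starting with endometrial ablation". No questionnaire step is placed between consent and randomisation. Research nurses check eligibility and counsel women before entry, and are responsible for collecting baseline data.
- **Interventions:** "The LNG-IUS can be placed either by a GP or by a gynaecologist", whereas the ablation is done by a gynaecologist. No section describes blinding.
- **Outcome measures:** "Secondary outcomes are patient satisfaction, complications, number of re-interventions, menstrual bleeding pattern, including rates of amenorrhea, QoL, sexual function, sick leave and costs". The Economic evaluation section bases QALYs on the SF-36.

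**The concern.** A baseline value can be used safely in a treatment comparison because allocation cannot have influenced it. That protection is lost if the value is recorded after the woman has learned her allocation. The instruments concerned are all self-reported. Relief, disappointment or anticipation of a procedure could change the answers, or affect whether the form is returned at all. The wait between randomisation and treatment may also differ between arms because providers and settings differ, although the article gives no waiting times.

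At stake are the secondary quality-of-life and sexual-function comparisons, any cost analysis adjusted for baseline, and the SF-36-based QALYs, in each case only where the analysis uses the baseline value. Randomisation offers no protection against a shift that arises after it, and a larger sample would not remove it.

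**Working it through.** **1. Timing rules side by side**

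| Instrument | Stated limit for baseline | Can it follow allocation? |
|---|---|---|
| PBAC | before randomisation | no |
| SF-36, Shaw | before start of treatment | yes |
| FSFI, FSDS, costs | none of their own; read from the preceding sentence | yes, on that reading |

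The recruitment section runs from consent to randomisation, and treatment follows. A form completed between randomisation and treatment meets the stated rule, and so does one completed before randomisation. No other section closes that window.

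**2. Does the woman know her allocation in that window?** The article does not use the term open-label. It is a safe inference: one arm receives a device and the other an ablation, no blinding is described, and "patients who are not satisfied with the (randomised) treatment effect can choose another treatment, or opt for hysterectomy".

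**3. Which analyses would carry a shift?** Suppose knowing the allocation moves one arm's mean baseline by s (in SD units), leaves follow-up scores unchanged, and the correlation of baseline with follow-up is rho (equal SDs).

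- Follow-up value compared without baseline: bias 0.
- Change from baseline: bias of size s.
- Baseline as covariate: bias of size rho × s.

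The article gives neither s nor rho. Over an assumed range:

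| s | change score | adjusted, rho 0.3 | rho 0.5 | rho 0.7 |
|---|---|---|---|---|
| 0.1 | 0.10 | 0.03 | 0.05 | 0.07 |
| 0.2 | 0.20 | 0.06 | 0.10 | 0.14 |
| 0.3 | 0.30 | 0.09 | 0.15 | 0.21 |

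The Data analysis section plans a mixed effects model for the effect over time and does not say how baseline enters it. If baseline is a covariate, the adjusted columns apply. If baseline is the first repeated measure and the effect is read as change from it, the change-score column applies.

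**4. QALYs.** Assume an area under the curve by the trapezium rule with SF-36 measurements at 0, 0.25, 0.5, 1 and 2 years. The baseline weight is 0.25/2 = 0.125 years, and the follow-up weights sum to 2 − 0.125 = 1.875 years. Take an assumed baseline utility shift d of 0.02 to 0.05.

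- No baseline adjustment: 0.125 × d = 0.0025 to 0.006.
- With baseline adjustment and an assumed slope of 0.5 at every visit: the regression coefficient is 0.125 + 0.5 × 1.875 = 1.0625. The net bias has size (1.0625 − 0.125) × d = 0.9375 × d, that is 0.019 to 0.047.

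The QALY effect is therefore very small without adjustment and several times larger with it. The article does not say which is planned.

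**5. What does not move.** PBAC at 24 months does not use these questionnaires, and its own baseline precedes randomisation. The planned 266 patients are unaffected by the timing of the forms.

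**The case against.** The strongest reply has four parts.

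- **The rule is also met by completion before randomisation.** Research nurses see the women before entry and handle baseline data, so that order is plausible in practice. This stands: a reader might infer that the baseline scores are post-randomisation measurements, and the article does not support that. It only allows it.
- **The different wording has an innocent explanation.** A PBAC score above 150 is an entry criterion, so the PBAC has to come first, while the questionnaires do not decide eligibility. That explains why the PBAC is singled out and shows no intention to collect the rest later. It does not close the window for the other forms.
- **An article condenses the full protocol, and a detailed visit schedule may be left to it.** This would answer a complaint about missing detail. Here, however, the article states a timing rule, and the rule as stated is looser than it needs to be.
- **The analyses that would be biased are not in the text.** Change scores and baseline-adjusted contrasts are not named; the article plans comparisons at 24 months, estimates at time points and a mixed model with unspecified handling of baseline. This also stands, and it makes the bias conditional. A reader might infer that every patient-reported secondary outcome is affected. That goes too far: patient satisfaction is not among the listed baseline questionnaires, PBAC is collected before randomisation, and follow-up sick leave and costs depend on baseline only if adjusted for it.

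**Conclusion.** The point holds as a weakness in a stated timing rule. The article lets the baseline SF-36 and Shaw questionnaires, and by natural reading the FSFI, FSDS and cost questionnaires, be completed after allocation is known. Analyses that use those values could then be biased.

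The size is unknown. The figures above (0.1 to 0.3 SD for a change score, 0.03 to 0.21 SD after adjustment) only translate assumed shifts and correlations. Nothing in the article indicates that a shift occurs, or in which direction, and these figures should not be cited as an estimate of bias in this trial.

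The conclusion rests on two readings: that the sexual-function and cost questionnaires share the limit of the sentence before them, and that women know their allocation. Both are inferred, the second safely. The primary outcome and unadjusted follow-up comparisons are untouched, so this is a worthwhile, inexpensive improvement to secondary and economic results and no threat to the main conclusion.

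**What to change.** - **Wording.** In Measurements and follow-up, state that the SF-36, Shaw, FSFI, FSDS and cost questionnaires are completed after written consent and before randomisation. They need not be completed at the same contact as the PBAC, which is an entry criterion and may predate consent.
- **Check.** Have the web-based randomisation program ask for confirmation that the forms are complete before it releases an allocation.
- **Women already enrolled.** Record the completion date of each baseline form and flag those completed after allocation. Run a sensitivity analysis that excludes those baselines or does not adjust for them.

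The cost is a small added step before randomisation, handled by research nurses who already see the women before entry. The sample size does not change. If practice already follows this order, correcting the sentence is enough.
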